## Abstract

**Background:**

The end tuberculosis (TB) strategy requires a novel patient treatment approach contrary to the one-size-fits-all model. It is well known that each patient’s physiology is different and leads to various rates of drug elimination. Therapeutic drug monitoring (TDM) offers a way to manage drug dosage adaptation but requires trained pharmacologists, which is scarce in resource-limited settings.

**Objective:**

We will develop an automated clinical decision support system (CDSS) to help practitioners with the dosage adaptation of rifampicin, one of the essential medical drugs targeting TB, that is known for large pharmacokinetic variability and frequent suboptimal blood exposure. Such an advanced system will encourage the spread of a dosage-individualization culture, including among practitioners not specialized in pharmacology. Thus, the objectives of this project are to (1) develop the appropriate population pharmacokinetic (popPK) model for rifampicin for Tanzanian patients, (2) optimize the reporting of relevant information to practitioners for drug dosage adjustment, (3) automate the delivery of the report in line with the measurement of drug concentration, and (4) validate and implement the final system in the field.

**Methods:**

A total of 3 teams will combine their efforts to deliver the first automated TDM CDSS for TB. A cross-sectional study will be conducted to define the best way to display information to clinicians. In parallel, a rifampicin popPK model will be developed taking advantage of the published literature, complemented with data provided by existing literature data from the Pan-African Consortium for the Evaluation of Antituberculosis Antibiotics (panACEA), and samples collected within this project. A decision tree will be designed and implemented as a CDSS, and an automated report generation will be developed and validated through selected case studies. Expert pharmacologists will validate the CDSS, and finally, field implementation in Tanzania will occur, coupled with a prospective study to assess clinicians’ adherence to the CDSS recommendations.

**Results:**

The TuberXpert project started in November 2022. In July 2024, the clinical study in Tanzania was completed with the enrollment of 50 patients to gather the required data to build a popPK model for rifampicin, together with a qualitative study defining the report design, as well as the CDSS general architecture definition.

**Conclusions:**

At the end of the TuberXpert project, Tanzania will possess a new tool to help the practitioners with the adaptation of drug dosage targeting complicated TB cases (TB or HIV, TB or diabetes mellitus, and TB or malnutrition). This automated system will be validated and used in the field and will be proposed to other countries affected by endemic TB. In addition, this approach will serve as proof of concept regarding the feasibility and suitability of CDSS-assisted TDM for further anti-TB drugs in TB-burdened areas deprived of TDM experts, including second-line treatments considered important to monitor.

**International Registered Report Identifier (IRRID):**

DERR1-10.2196/58720

## Introduction

Even though tuberculosis (TB) is curable, it remains one of the leading causes of death from a single bacterial infection worldwide. The World Health Assembly declared the end of TB with a drastic reduction in death and incidence; however, the decrease is at a suboptimal pace, only 11% and 9.2%, contrary to at least 20% and 35% by 2020, respectively [1,2]. Sub-Saharan Africa contributes around 25% of the global TB burden, with a higher death rate than other World Health Organization (WHO) regions at 22% [3]. Significant and commonly coexisting comorbidities in patients with TB, which include HIV coinfection [4], enteric pathogens [5], malnutrition [6], and diabetes mellitus (DM) [7], increase the risk of unfavorable treatment outcomes. This is primarily driven by incomplete adherence and pharmacokinetic variability of first-line antitubercular (anti-TB) drugs, leading to insufficient circulating drug exposure and development of drug-resistant TB or excessive exposure and toxicity, resulting in treatment interruption.

Precision dosage of medicines based on drug concentration monitoring is an essential patient-centered approach for optimizing adherence and efficacy and preventing adverse effects. There are available tools for helping pharmacologists with the dosage adaptation process. However, they are difficult to use for nonspecialists and would benefit from automation. Real clinical decision support systems (CDSS), that have the potential to assist practitioners, not necessarily pharmacologists, in the dosage adaptation of anti-TB drugs in patients with TB, are yet to be available in TB endemic settings. Deployment of such an advanced system will encourage the spread of a dosage-individualization culture among practitioners not specialized in pharmacology while bridging the gap by adapting those novel technologies for optimizing TB care [8].

In that context, as part of the Adaptive Diseases Control Expert Programme in Tanzania, the TuberXpert project aims to develop an automated CDSS to help practitioners with the dosage adaptation of rifampicin. Being one of the essential medical drugs targeting TB, rifampicin is known for its significant pharmacokinetic variability and frequent suboptimal blood exposure [9].

This project shows the field application of such an automated CDSS for the dosage adaptation of rifampicin in Tanzania with underpinned applied research questions to address scientific implementation for sustainability. The 3 project partners are the University of Applied Sciences and Arts Western Switzerland (HEIG-VD), the University Hospital of Lausanne (CHUV), and the Kibong’oto Infectious Disease Hospital (KIDH). HEIG-VD is bringing computer science expertise, CHUV pharmacometrics expertise, and KIDH clinical expertise.

## Methods

### Overview

An automated CDSS software requires an embedded population pharmacokinetic (popPK) model for rifampicin to predict drug concentrations and propose meaningful adjustments correctly. The software will be based on the core computing engine of Tucuxi [10,11], a model-informed precision dosing software for Bayesian forecasting that was already developed and that helps clinicians adapt medical drug dosages. These software computations are based on the popPK models implemented within the software and the model-identified influential patient covariates, potential drug concentration measurements, and specific drug pharmacokinetics (PK) targets validated by therapeutic drug monitoring (TDM) experts for dose optimization. The CDSS will be implemented in 5 phases, as shown in Figure 1. In brief, the first phase includes developing an appropriate popPK model for rifampicin for Tanzanian patients and implementing it within Tucuxi. The second phase will optimize reporting relevant information to practitioners for drug dosage adjustment. The third phase will automate the delivery of the report in line with the measurement of the drug concentration [12]. The fourth phase will validate the system, and the final step will implement the system in the field. Details of each stage and associated research questions are summarized in the next subsections.

**Figure 1 figure1:**
[figure not shown]
TuberXpert protocol PERT diagram decomposed into 5 phases. CDSS: clinical decision support system; popPK: population pharmacokinetic; panACEA: Pan-African Consortium for the Evaluation of Antituberculosis Antibiotics; PERT: program evaluation and review technique; TDM: therapeutic drug monitoring.

### Model Selection, Development, and Calibration

Predicting the concentration of a medical drug in blood for dosage adjustment using Tucuxi crucially requires the selection of a popPK model, as the latter determines the ability of the software to propose the correct dosage regimen for each patient. An extensive literature search will be conducted to identify the published popPK models of rifampicin in patients with TB [13-15], developed using NONMEM (ICON) [16] or Monolix (Lixoft) [17], both widely used computer programs for parametric popPK analyses. Models describing rifampicin PK in patients with TB with the previously mentioned comorbidities, that is, DM, malnutrition, and HIV, will be included to investigate their impact on the anti-TB drug PK. The number of participants in the studies, as well as that of available observations distributed over time, will be considered. The description of the model development steps (eg, structural and statistical considerations, and inclusion of covariates) will be carefully reviewed, and the study results will be judged using standard procedures in population analysis (eg, diagnostic goodness-of-fit plots and type of validation) to ensure the quality of the model and the completeness of the information provided. The available models will be ranked according to a cumulative score based on the previous elements, and the best one will be selected for implementation. Because of the autoinduction and the nonlinear processes underlying rifampicin absorption and elimination, we expect a complex nonlinear popPK model to characterize its PK best (which will require software updates to encompass specific kinetics). If the best-identified model fails to capture essential PK characteristics of rifampicin, the opportunity to use a model-based meta-analysis approach will be investigated to build a comprehensive popPK model using all available pertinent literature. Model refinement will be attempted if the selected model proves to be computationally prohibitive for its implementation in Tucuxi, verifying that the simplified model’s prediction for the targeted exposures is comparable to the original ones. Whatever the choice made for this step, the model will undergo formal validation and adjustment to Tanzanian patients using rifampicin concentrations available through the Pan-African Consortium for the Evaluation of Antituberculosis Antibiotics (panACEA) network and those collected in Tanzania within this project. To achieve this aim, a prospective study will be conducted on 50 patients with TB (including those with HIV coinfection, coexistent DM, or malnutrition) followed at the KIDH or in neighborhood clinics during the early stage of the TuberXpert project. These patients will provide 3 samples randomly on 2 separate occasions, that is, at the treatment start and approximately after 1 week of treatment. We will elaborate and then strictly follow a study protocol. We will also conduct a study comparing dried blood spot analysis [12] to HPLC-UV laboratory analysis [18] on these samples. Finally, we will conduct a Delphi study, as suggested in reference [19], to define the optimal therapeutic target, as this is critical for therapy individualization and there is currently no definitive consensus for rifampicin (various propositions [13,20-22]).

Before using Tucuxi in therapy individualization, we have to conduct further essential preliminary validation step. It will consist of verifying that the dosage regimen propositions made by the software are in line with those made by experienced pharmacologists to perform TDM in their clinical practice. Pharmacologists of the service of clinical pharmacology of CHUV and clinicians at KIDH will be in charge of such clinical validation of the software using selected patients of this study. Data on rifampicin dosage history and concentrations, administration, and sampling times, and all necessary clinical information on the selected patients will be collected. Experienced pharmacologists will choose the most appropriate dosage regimen to achieve the target according to the patient clinical status among those proposed by the software using the graphical user interface (GUI) of Tucuxi. The correctness of the forecasted dosing schedule will be validated against the dosage recommendations made by the TDM experts at CHUV and clinicians at KIDH. After this vital validation step, the model will be made available within the standalone Tucuxi software, allowing users to exploit this new model.

The research question components are as follows: (1) What is the appropriate popPK model that includes the structural and statistical considerations, as well as the influential individual factors, to be incorporated in Tucuxi for optimizing rifampicin dosage in patients with TB in Tanzania? (2) What is the Tucuxi-guided rifampicin dosage adjustment accuracy for anti-TB therapy individualization against experienced pharmacologists in the TDM clinical practice?

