## Results

The TuberXpert project started in November 2022. During its first phase, and as of July 2024, a total of 50 patients have been enrolled to gather the required data to build a popPK model for rifampicin. In addition, the panACEA consortium agreed to share and already provided individual rifampicin data collected in three different studies (trial numbers NCT01392911, NCT00760149, and NCT01785186), allowing preliminary popPK model development based on these data. A review of TDM practices for TB treatment in Tanzania has also been conducted within the same timeframe. From January to December 2023, we carried out the report design study. We started with a literature review concerning the best way to present information to clinicians. Then we created mock-up reports and conducted a qualitative study with 2 rounds of interviews (13 Tanzanian and 27 non-Tanzanian clinicians) to end up with the final report layout. In September 2023 we started to CDSS general architecture. In July 2024 the first prototype of the CDSS core system was finalized.

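### Measured concentrations play no part in ranking the candidate models, and correctness of the dosing forecast rests on expert agreement; an out-of-sample forecast of the week-1 concentrations would test it directly

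*Protocol article*

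**What the plan says.** Everything here is in the protocol article. The main section is Methods, Model Selection, Development, and Calibration.

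- **Choosing a model.** Published models are assessed on numbers of participants and observations, the description of model development, published fit diagnostics and the way each model was validated. Then: "The available models will be ranked according to a cumulative score based on the previous elements, and the best one will be selected for implementation". A model-based meta-analysis is the fallback if the best model misses essential features of rifampicin kinetics. A simplified model must predict comparably to the original.
- **Use of concentrations.** Whatever model is chosen, "the model will undergo formal validation and adjustment to Tanzanian patients using rifampicin concentrations available through the Pan-African Consortium" and those collected in this project. For this purpose "a prospective study will be conducted on 50 patients with TB". On sampling: "These patients will provide 3 samples randomly on 2 separate occasions, that is, at the treatment start and approximately after 1 week of treatment".
- **Correctness of the dosing forecast.** A further validation step follows: "The correctness of the forecasted dosing schedule will be validated against the dosage recommendations made by the TDM experts at CHUV and clinicians at KIDH". The experienced pharmacologists choose the most appropriate regimen "among those proposed by the software using the graphical user interface (GUI) of Tucuxi". After this step the model is released in the standalone software. The second research question asks for accuracy relative to experienced pharmacologists.
- **Later validation.** In the System Validation section the reference is again an expert report, prepared by hand in the same software, and the population model is treated as already validated.
- **Data status.** The Results section reports that "a total of 50 patients have been enrolled to gather the required data to build a popPK model for rifampicin", and that panACEA "agreed to share and already provided individual rifampicin data collected in three different studies".

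**The concern.** The tool takes early concentrations, predicts later ones and derives a dose. Three stated choices weaken the evidence that it does this well.

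First, the ranking asks how well a model was developed and reported elsewhere, not how well it predicts these patients. A well-documented model may still predict Tanzanian patients with HIV, diabetes or malnutrition poorly. The concentrations that could show this are used only after selection.

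Second, the same concentrations serve for adjustment and validation, and no separation is stated. A model checked on the data that tuned it looks better than it is.

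Third, a forecast is a claim about later concentrations, and agreement with a recommendation does not test that claim. When the pharmacologist chooses from options that the model generated, a biased model shifts both the options and the choice, and agreement can stay high. The System Validation stage repeats this arrangement, so it is not set up to expose model error either.

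At stake is a model released for dose individualisation without direct evidence on the size and direction of its forecast error in the target population.

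**Working it through.** The article gives no power, precision or acceptance figure for this step, so there is no stated figure to reproduce. The check sets the statements side by side and then asks what the planned sample could show.

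**Step 1. What each stage is compared with**

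| Stage | Compared with | Can it reveal forecast bias? |
|---|---|---|
| Ranking of published models | Literature features | No; no project or panACEA concentration enters |
| Formal validation and adjustment | Measured concentrations | Yes, if validation data are kept apart from adjustment data; not stated |
| Correctness of the dosing schedule | Expert and clinician recommendations | Weakly; pharmacologists choose within the software's proposals |
| System validation | Manual expert report made in the same software | Weakly, for the same reason |

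No section describes forecasting the second occasion from the first.

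**Step 2. Is such a forecast feasible?** The software performs Bayesian updating from a patient's own observations (CDSS section), and the design has two occasions. The sampling sentence can be read in two ways:

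- three samples per occasion: 50 × 3 × 2 = 300 in all, of which 50 × 3 = 150 fall on the second occasion;
- three samples per patient: 50 × 3 = 150 in all.

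Either reading allows a forecast, though the second leaves fewer samples per occasion.

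**Step 3. What precision would it give?** Take one summarised relative prediction error per patient, so that patients are the independent units.

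- 95% half-width for mean bias = t(0.975, n − 1) × SD / √n
- Approximate power to detect a 20% mean bias, two-sided 5% = Φ(0.20 / (SD/√50) − 1.96)

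The SD is an assumption, varied from 0.20 to 0.60. The 20% bias is illustrative. For SD 0.30: 2.010 × 0.30/√50 = 0.085 with n = 50, and 2.064 × 0.30/√25 = 0.124 with n = 25.

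| Assumed SD | Half-width, n = 50 | Half-width, n = 25 held out | Power for 20% bias, n = 50 |
|---|---|---|---|
| 0.20 | 5.7% | 8.3% | >99% |
| 0.30 | 8.5% | 12.4% | >99% |
| 0.40 | 11.4% | 16.5% | 94% |
| 0.50 | 14.2% | 20.6% | 81% |
| 0.60 | 17.1% | 24.8% | 65% |

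The n = 50 column needs all 50 patients to be evaluable. It applies approximately under cross-validation, where every patient is forecast by a model fitted without that patient. The n = 25 column shows the price of a single half-and-half split.

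**The case against.** The strongest reply is that measured concentrations are already used to test the model. The article plans formal validation on panACEA and project data, says that the 50-patient study serves this aim, and presents the expert comparison as an additional step. That is right. A reader might infer that the model is never checked against observed concentrations, and the documents do not support this. What remains is that these data come after the ranking and that adjustment and validation are not separated.

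Other replies also carry weight:

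- **The accuracy question.** A reader might infer that it goes unanswered. It does not, because the question defines accuracy relative to pharmacologists. The criticism is of that definition.
- **The literature score.** It is not the only determinant. There are the fallback, the check on simplified models, the later adjustment, and a model being built from the acquired data (Results; Future Directions).
- **Missing metrics.** The article announces a separate study protocol. Prediction-error measures, data splits and acceptance limits may be there, and their absence from an article is not an error.
- **What the forecast would prove.** A reader might take it as evidence that exposure is on target after a dose decision. No dose decision is described between the two occasions, so it would not show that. The Implementation in the Field section plans to look at outcomes after adjustment.
- **Circularity.** It is partial. The article describes the choice among software proposals for the pharmacologists and does not say how KIDH clinicians form their recommendations. It shows that agreement could be high despite bias, not that it will be.
- **Sources of error.** Because the article expects autoinduction, a start-to-week-1 error mixes the induction component with the individualisation. The tool needs both, but the test alone would not separate them.

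These points narrow the finding. They do not answer the literature-only ranking or the use of expert agreement as the test of a correct forecast.

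**Conclusion.** The point holds in a limited form. Concentration-based validation is planned, but the data enter only after models are ranked and selected on literature features, and the article states no separation between data for adjustment and data for validation. Correctness of the dosing forecast is then judged by agreement with recommendations, with pharmacologists selecting from the software's own options.

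A better method is available within the planned design. Under the assumed SD range of 0.20 to 0.60, an out-of-sample forecast would estimate mean bias to within about 6% to 17% with 50 evaluable patients and about 8% to 25% with 25 held out. At the upper end of that range, a single split gives only a coarse answer, which favours cross-validation.

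These figures rest on the assumed SD and on patients having usable samples on both occasions. The article reports enrolment of 50 patients and receipt of the panACEA data, but not completed assays or samples per patient. It does not say whether the panACEA data cover two occasions. This is a recommended improvement in method, not an error that invalidates the project.

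**What to change.** 1. **Model choice.** Keep the literature score as a screen. Choose among the top-ranked published models and the team's own model by bias and RMSE on panACEA and Tanzanian concentrations, before any re-estimation. Score the team's own model only on data not used to build it.
2. **Formal validation.** Forecast each patient's second-occasion concentrations twice: from covariates alone, and from covariates plus first-occasion data. Use cross-validation or patients held out from the adjustment. Report mean prediction error and RMSE with confidence intervals, with the patient as the unit. The difference between the two forecasts shows what the early samples add. Add correct classification against the target once the Delphi study has set one.
3. **Expert comparison.** Have experts record their recommendation before seeing the software's proposals, and report the result as agreement or clinical plausibility, not as correctness of the forecast.
4. **Reporting.** State whether three samples are taken per occasion or per patient, and how many patients have usable samples on both occasions.

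The cost is analyst time and the coding of several candidate models instead of one. Asking experts to recommend first changes the order of their work. No new patients or samples are needed. The result will describe concentration forecasts, with induction and individualisation together; exposure after a dose change remains a question for the field phase.
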